
### Participant timeline

A schematic diagram highlighting the time schedule of enrolment, interventions, and assessments is presented in Fig. 1.

**Fig. 1 Fig1:**
[figure not shown]
Schedule of enrolment, interventions, and assessments

### Sample size and power analysis

The sample size calculations were based upon the primary outcome of reduction exposure to ESA. For Aim 1, we anticipate an average reduction of 0.3 days (SD = 3.5 days) of exposure to ESAs due to rapid diagnostic testing, based on our preliminary data. To achieve 83% power to detect this effect size at a two-sided alpha of 0.05 and an intra-cluster correlation (ICC) of 0.001, we will randomize 12 hospitals (6 in the rapid diagnostic testing arm and 6 in the control arm) with an average of 1000 patients per hospital (coefficient of variation (COV) = 0.4). This will result in a total sample size of 12,000 patients (6000 patients per arm).

For Aim 2, we will compare the six hospitals implementing pharmacist-led antimicrobial de-escalation and the other six hospitals serving as the control group. De-escalation is expected to reduce exposure to ESAs by 1 day (SD = 3), based on our preliminary data. Assuming a 50% compliance rate in the de-escalation arm, we will have > 99% power to detect this effect size at a two-sided alpha of 0.05 and an ICC of 0.005. We will also have > 99% power to detect a reduction in the rates of CDI from 1 to 0.5% and AKI from 6 to 3%, under the same assumptions. Since testing the interaction is a secondary analysis, power calculation was not performed. All power calculations were conducted using PASS 14 (Kaysville, UT).

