De-escalation following negative bacterial cultures is another antimicrobial stewardship target. While most de-escalation follows the identification of a susceptible pathogen, the IDSA/ATS guidelines also recommend de-escalation to a narrower spectrum at 48 h if cultures are negative [6]. However, this recommendation is based on observational studies. In our study of 164 US hospitals, we found that de-escalation practices following negative cultures varied widely by hospital, and no hospital de-escalated even 40% of eligible patients [14]. De-escalation was associated with shorter length of stay and lower rates of inpatient mortality. A hospital-wide pharmacist-led effort to encourage physicians to follow the ATS/IDSA guidelines and de-escalate after 48 h could help overcome fears about resistant pathogens and treatment failure.

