### Participating sites

Enrolling sites will include ten hospitals in Northeast Ohio (Cleveland Clinic Main Campus, Fairview Hospital, Hillcrest Hospital, Marymount Hospital, Akron General Hospital, Avon Hospital, Euclid Hospital, Lutheran Hospital, Medina Hospital, and South Pointe Hospital) and two from Florida (Weston and Indian River Hospital) (Table 2). Hospitals will be divided into 3 strata based on teaching status, size of the hospital, and number of CAP patients with each stratum containing 4 hospitals. The hospitals will then be randomized to each of the 4 trial arms with an effective sample size of 3 hospitals in each arm.

**Table 2 Tab2:** Enrolling hospital sites by bed size and teaching status

Hospital	Number of beds	Residency program
Cleveland Clinic Main Campus	1167	Yes
Fairview General Hospital	488	Yes
Hillcrest Hospital	341	No
Marymount Hospital	195	No
Akron General	532	Yes
Avon Hospital	126	No
Euclid Hospital	110	No
Lutheran Hospital	119	Yes
Medina Hospital	148	No
South Pointe Hospital	167	Yes
Cleveland Clinic Florida, Weston Hospital	230	Yes
Indian River Hospital	332	No

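### Aim 1's 83% power holds only at an ICC of 0.001, while Aim 2 assumes 0.005 for the same outcome in the same 12 hospitals, with no reason given

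*Protocol article*

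**What the plan says.** All statements are in the protocol article, Sample size and power analysis, unless another section is named.

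- One outcome drives the calculations: "The sample size calculations were based upon the primary outcome of reduction exposure to ESA".
- Aim 1 effect and SD: "For Aim 1, we anticipate an average reduction of 0.3 days (SD = 3.5 days) of exposure to ESAs".
- Aim 1 power and ICC: "To achieve 83% power to detect this effect size at a two-sided alpha of 0.05 and an intra-cluster correlation (ICC) of 0.001".
- Clusters: "we will randomize 12 hospitals (6 in the rapid diagnostic testing arm and 6 in the control arm". Mean cluster size is taken as 1000, and the COV of cluster size as 0.4.
- Aim 2 compares six of these hospitals with the other six on the same outcome. It takes a 1-day reduction with SD 3 and is powered "at a two-sided alpha of 0.05 and an ICC of 0.005".

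The effects are attributed to preliminary data. Neither ICC has a source, and the text does not say why the ICC and SD differ between aims.

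Under Data analysis plan, the ITT analysis takes eligible patients from all randomized hospitals. Days on ESA are analysed in a linear mixed model with a random intercept for hospital, adjusted for patient covariates and for hospital characteristics in the prior year, including ESA duration.

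**The concern.** An ICC describes an outcome in a population of patients and hospitals, not an intervention. Both aims use the same outcome, hospitals and ITT population, so a reader expects one SD and one ICC, or a stated reason for two. The section gives two pairs and no reason.

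The gap matters mainly for Aim 1. Its anticipated effect is 0.3 days. An ICC of 0.001 with SD 3.5 implies a between-hospital SD of 3.5 × √0.001 = 0.11 days; an ICC of 0.005 implies 3.5 × √0.005 = 0.25 days, close to the whole effect. With six hospitals per side, the difference between these two values decides whether Aim 1 is adequately powered. The article presents 83% as a single figure with no sensitivity to the ICC, so a reader cannot see how much it depends on this one input.

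**Working it through.** **Inputs** (Sample size and power analysis): k = 6 hospitals per side, mean cluster size m = 1000, CV = 0.4, difference δ = 0.3 days, SD σ = 3.5, two-sided α = 0.05.

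**Method.** The article does not state the design-effect formula, so two common forms for unequal cluster sizes were used:

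- A (relative efficiency): DE = [1 + (m − 1)ρ] / [1 − CV²·L(1 − L)], with L = mρ / (mρ + 1 − ρ)
- B: DE = 1 + [(1 + CV²)m − 1]ρ

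Then SE = σ√(2·DE / (k·m)), ncp = δ / SE, and power comes from the non-central t with 2k − 2 = 10 df (critical value 2.228).

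**Reproducing the plan's figure, ρ = 0.001**

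- A: L = 1/(1 + 0.999) = 0.500; DE = 1.999 / (1 − 0.16 × 0.25) = 2.08; SE = 3.5 × √(2 × 2.08/6000) = 0.092; ncp = 3.25; power 83.4%.
- B: DE = 1 + (1160 − 1) × 0.001 = 2.16; SE = 0.094; ncp = 3.20; power 82.1%.

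Both agree with the stated 83%. A normal approximation on the same design effects gives 89–90% and does not, so the stated figure is consistent with a t test on cluster-level degrees of freedom.

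**Changing only the ICC**

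| ICC | DE (A / B) | SE (A / B) | ncp (A / B) | Aim 1 power (A / B) |
|---|---|---|---|---|
| 0.001 | 2.08 / 2.16 | 0.092 / 0.094 | 3.25 / 3.20 | 83% / 82% |
| 0.002 | 3.11 / 3.32 | 0.113 / 0.116 | 2.66 / 2.58 | 67% / 64% |
| 0.003 | 4.12 / 4.48 | 0.130 / 0.135 | 2.31 / 2.22 | 55% / 52% |
| 0.005 | 6.13 / 6.80 | 0.158 / 0.167 | 1.90 / 1.80 | 40% / 37% |

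**Using Aim 2's SD and ICC together** (σ = 3, ρ = 0.005): SE 0.136 / 0.143, ncp 2.21 / 2.10, power 52% / 48%.

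**Sensitivity to method at ρ = 0.005, σ = 3.5.** Ignoring the CV gives 41% (10 df); 8 or 9 df with the CV gives 35–40%; the normal approximation gives 44–48%. No variant reaches 50%.

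**Would more patients help?** As m grows without limit, SE tends to σ√(2ρ/k) = 3.5 × √(0.01/6) = 0.143, so ncp = 2.10 and power is about 48%. At ICC 0.005 and SD 3.5, the number of hospitals is the limit, not the number of patients.

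**The case against.** Nothing is miscalculated: 83% follows from its own inputs. That stands, and the point is about inconsistent assumptions, not arithmetic.

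The two pairs may come from different preliminary samples. Pharmacist-led de-escalation acts on clinically stable patients with negative cultures beyond 48 h, and Aim 2's SD and ICC may have been estimated in that subset. This is possible, but the article does not say so. The planned analysis takes all eligible patients, so a subset value would itself need justifying.

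Adjustment for prior-year hospital ESA duration, with stratification by hospital type, may lower the residual ICC. As an illustration (assumption), if it removed half the between-hospital variance from an ICC of 0.005, the residual would be about 0.0025 and Aim 1 power 57–61%; if it removed 80%, the residual would be about 0.001 and power 82–83%. So 37–40% is not necessarily the power of the adjusted model. But the adjustment applies to both aims and cannot explain why their ICCs differ.

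Three stronger readings are tempting, and the document supports none of them:

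- *Aim 1's true power is 37–40%.* Both ICCs are the plan's own. The larger may be a cautious value chosen where the effect is large; adopting the smaller for both aims would leave the 83% intact.
- *The background shows that the smaller ICC is wrong.* The remark that "de-escalation practices following negative cultures varied widely by hospital" concerns de-escalation rates in 164 US hospitals. It does not concern ESA days in 12 hospitals of one health system.
- *The COV of 0.4 is wrong.* Table 2 ("Enrolling hospital sites by bed size and teaching status") gives a CV of bed numbers of 0.87–0.91, but beds are only a proxy for pneumonia admissions. One 1167-bed hospital drives the figure; without it the CV is 0.56–0.59.

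**Conclusion.** The concern holds as an unexplained inconsistency in planning inputs. For one primary outcome in one set of hospitals, the section uses ICC 0.001 with SD 3.5 and ICC 0.005 with SD 3. Aim 1's stated power depends on the first pair. Over the plan's own ICC range it runs from 82–83% down to 37–40% at SD 3.5, and under Aim 2's pair it is 48–52%.

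These figures assume 6 against 6 hospitals, a mean of 1000 patients, COV 0.4, a 0.3-day effect and a t test on 10 df, and they credit no further variance reduction from covariates. The document cannot show which ICC applies, or what the residual ICC will be after adjustment. The supported conclusion is therefore that 83% should not stand alone, not that some lower figure should replace it.

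**What to change.** 1. Use one SD and one ICC for ESA days in both aims, with their source, or state why they differ. If the ICC is meant to be residual after adjustment for prior-year hospital ESA use, say so and apply it to both aims.
2. Replace the single 83% with Aim 1 power across ICC 0.001–0.005, for example the four rows tabulated above, naming the design-effect formula and degrees of freedom.
3. Leave the sample size as it is.
4. As a minor check, compare the COV of 0.4 with the pneumonia admission counts that were used to select the hospitals.

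The cost is a few lines of text and a less favourable picture for Aim 1. No outcome, model, test or enrolment target changes.

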#### Pharmacist-led de-escalation

Another algorithm will identify CAP patients meeting study criteria with negative culture results for more than 48 h, generating a list for the clinical pharmacist. The pharmacist will audit the daily alerts on weekdays at a centralized location and assess patient clinical stability using the 2019 ATS/IDSA criteria for clinical stability:A.Resolved vital sign abnormalities (temperature ≤ 37.8 °C, heart rate ≤ 100 beats/min, arterial oxygen saturation ≥ 90% or pO_2_ ≥ 60 mmHg on room air, systolic blood pressure ≥ 90 mmHg, and respiratory rate ≤ 24 breaths/min),B.Normal mental status (as deemed by the clinician), andC.Ability to maintain oral intake [6].

For clinically stable patients, the pharmacist will recommend antimicrobial de-escalation to clinical providers via secure electronic medical record chat, phone call, or page. De-escalation in this context means stopping all ESA agents (anti-MRSA/anti-pseudomonal) but continuing other antibiotics. The pharmacist’s recommendations will be based on a protocol developed by the Cleveland Clinic Health System’s Antimicrobial Stewardship committee, outlining four possible clinical scenarios: (a) positive culture, (b) negative culture, (c) pneumococcal UAT results, and (d) viral test results.

Pharmacist-led de-escalation efforts will be supported by educational initiatives targeting hospitalists, including presentations about the study and audit-and-feedback for adherence to pharmacist recommendations. Site champions at each hospital will ensure intervention fidelity and encourage physician receptiveness to pharmacist messages/calls.

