## Statistical methods

### Data analysis plan

The data analysis will be conducted following the intention-to-treat (ITT) principle which includes 3 rules. The first rule establishes the landmark event for entry into the study, which is the randomization of hospitals. All randomized hospitals will be considered enrolled, and data of eligible patients treated by enrolled hospitals will be analyzed. The second rule establishes patient-level data collection, which is independent of treatment assignment. The third rule defines the pre-specified time period for counting study events, which varies for each outcome.

We will follow the order principle of analyses, which states that analyses involving the primary outcome measure must be preceded by analyses of higher-order outcomes when those outcomes are censored. In our study, all-cause death events are censored. To follow the order principle of analyses, we will compare the all-cause mortality incidence rate within the first 30 days of admission across the four treatment groups. Incidence rate is calculated as the number of all-cause deaths divided by the number of included patients and expressed per 1000 (or 10,000 patients) per 30 days of follow-up. We will calculate the incidence-rate difference between the four treatment groups, using the usual care group as the reference. The four treatment arms are rapid testing and de-escalation, rapid testing only, de-escalation only, and usual care (i.e., neither rapid testing nor de-escalation).

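### The Aim 2 power of over 99% reproduces only if the full 1-day reduction applies to every analysed admission; a 1-day effect per de-escalated patient gives about 88–91% at the stated 50% compliance, and less after other dilution

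*Protocol article*

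**What the plan says.** The section on sample size and power describes the Aim 2 contrast as follows: "we will compare the six hospitals implementing pharmacist-led antimicrobial de-escalation and the other six hospitals serving as the control group". The effect is given as "De-escalation is expected to reduce exposure to ESAs by 1 day (SD = 3), based on our preliminary data". The remaining inputs are "Assuming a 50% compliance rate in the de-escalation arm" and "two-sided alpha of 0.05 and an ICC of 0.005", and the stated result is power above 99%. Cluster size is given under Aim 1: "with an average of 1000 patients per hospital (coefficient of variation (COV) = 0.4".

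Three other places bear on what that effect can be:

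- **Who can be reached.** The section on pharmacist-led de-escalation says: "Another algorithm will identify CAP patients meeting study criteria with negative culture results for more than 48 h". The pharmacist then makes a recommendation only for clinically stable patients, and de-escalation is defined as stopping the ESA agents, so a patient must be on one.
- **Who is analysed.** The data analysis plan says: "All randomized hospitals will be considered enrolled, and data of eligible patients treated by enrolled hospitals will be analyzed". The eligibility criteria do not require ESA use, a negative culture or stability at 48 h.
- **What happens without the intervention.** The control section leaves usual care in place. The background reports from 164 US hospitals that "de-escalation practices following negative cultures varied widely by hospital, and no hospital de-escalated even 40% of eligible patients".

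**The concern.** The sentence giving the effect attributes the 1 day to de-escalation, which reads most naturally as the effect in a patient who is de-escalated. The primary analysis instead compares mean ESA days over all eligible admissions. Between the two lie three dilutions: recommendations not followed, patients whom usual care would have de-escalated anyway, and admissions with nothing to de-escalate. Only the first is mentioned, and the printed power does not appear to reflect it.

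Hypothesis 2a is one of the trial's main hypotheses. If its power is overstated, a null result could be read as showing that pharmacist-led de-escalation does not reduce ESA use, when the expected effect may have been too diluted to detect reliably. The protocol also plans to stop for futility when conditional power falls below 0.2 at the halfway point, and a diluted effect makes that more likely than readers of the printed figure would expect.

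**Working it through.** **Inputs.** Six hospitals per arm (k = 6), mean size m = 1000, two-sided alpha 0.05; Aim 1: 0.3 day, SD 3.5, ICC 0.001; Aim 2: 1 day, SD 3, ICC 0.005, compliance 50%. The coefficient of variation of cluster size (CV = 0.4) is printed for Aim 1 and assumed to carry over to Aim 2.

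**Formulas.** SE = SD × √(2 × DE / (k × m)). Power is from the noncentral t with 2 × 6 − 2 = 10 df, noncentrality effect/SE; the normal approximation is shown for comparison. Two standard design effects for unequal clusters:

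- Method A: DE = 1 + ((1 + CV²)m − 1) × ICC.
- Method B: DE = (1 + (m − 1) × ICC) / RE, with RE = 1 − CV² × λ(1 − λ) and λ = m × ICC / (m × ICC + 1 − ICC).

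**Calibration on Aim 1 (printed power 83%).**

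- A: DE = 1 + 1159 × 0.001 = 2.159, SE = 0.0939, 0.3/SE = 3.20, power 82.1%.
- B: DE = 1.999/0.960 = 2.082, SE = 0.0922, 0.3/SE = 3.25, power 83.4%.

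Both come within one point of the printed figure with t on 10 df. The normal approximation gives 89–90%, so t is the better match to the protocol's own method.

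**Aim 2.**

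- A: DE = 1 + 1159 × 0.005 = 6.795, SE = 3 × √(2 × 6.795/6000) = 0.143 day.
- B: DE = 5.995/0.978 = 6.131, SE = 0.136 day.

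| Reading | Mean difference over all admissions | Power, t (A / B) | Power, normal (A / B) |
|---|---|---|---|
| Full 1 day in every admission | 1.00 day | >99.9% / >99.9% | >99.9% / >99.9% |
| 50% compliance only | 1 × 0.50 = 0.50 | 88% / 91% | 94% / 96% |
| Plus 20% usual-care de-escalation; compliance = acceptance among those still on an ESA | 0.50 × (1 − 0.20) = 0.40 | 71% / 76% | 80% / 84% |
| Plus 20% usual-care de-escalation; 50% = total share de-escalated | 0.50 − 0.20 = 0.30 | 48% / 52% | 56% / 60% |
| 50% compliance, no usual-care de-escalation, half of admissions candidates | 0.50 × 0.50 = 0.25 | 35% / 38% | 42% / 45% |

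The 20% usual-care rate and the 50% candidate share are assumptions for illustration. The document gives neither for these hospitals.

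**What more than 99% requires.** An all-admission difference of roughly 0.6 day (normal) to 0.7 day (t) is needed for 99% power. With 0.5 day and equal cluster sizes (CV = 0) power is still 92% (t) or 96% (normal). A 0.5-day effect exceeds 99% if Aim 1's ICC of 0.001 replaces the stated 0.005 (99.98%, t).

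**The case against.** The strongest defence is that the 1 day may already be the net difference between arms. The preceding sentence sets up a comparison of six hospitals with six, and the figure is said to come from preliminary data. A reader could also take it as the effect after allowing for 50% compliance. On either reading more than 99% reproduces and usual-care de-escalation is already netted out. A journal article may leave the derivation of an effect size to the full protocol. This stands as a possibility, and the text does not settle it. But on that reading the compliance clause does no work where it is placed, and the sentence credits the day to de-escalation rather than to the programme.

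A reader might infer more than the article supports:

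- **That the plan assumed no usual-care de-escalation and made every admission a candidate, and so reached its figure.** The zero rate would be inferred from silence. Those two assumptions with 50% compliance give 88–91%, so they do not explain the printed power.
- **That usual care here de-escalates close to 40%, leaving almost no power.** The background figure is a ceiling that none of 164 other hospitals reached. No mean is given, and it does not estimate the rate in the control hospitals. It shows only that the rate matters.
- **That 50% minus the usual-care rate is the right multiplier.** It is one reading. The protocol elsewhere speaks of adherence to pharmacist recommendations, which favours the milder 0.50 × (1 − usual-care rate).
- **That the trial is too small.** The candidate share is unknown, and the 12,000 patients were derived under Aim 1.

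The planned complier average causal effect, as-treated and per-protocol analyses give some protection against misreading a null result caused by non-adherence. They do not deal with admissions that were never candidates, and they do not make the printed power correct.

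**Conclusion.** The concern holds as a power statement that does not follow from the inputs printed beside it, unless the 1 day is an undiluted difference over every analysed admission. If it is the effect per de-escalated patient, the stated compliance alone brings power to about 88–91% by the method that reproduces Aim 1. Any usual-care de-escalation, or any candidate share below 100%, takes it lower. How much lower cannot be fixed from the article: the 71–76%, 48–52% and 35–38% results rest on assumed rates. All figures also assume that the Aim 1 cluster size and its variation apply to Aim 2 and that the SD remains 3. The article does not support the claim that Aim 2 is badly underpowered; it supports only that the printed assurance is not established.

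**What to change.** In the sample size and power section, state whether 1 day is the effect per de-escalated patient or a net arm-level difference over all admissions.

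- **If per patient:** recompute power with the compliance, usual-care de-escalation rate and candidate share (on an ESA, culture-negative and stable after 48 h) taken from the 12 hospitals' prior-year data. Define compliance as either acceptance of a recommendation or the total share de-escalated. Show a range and replace the printed figure.
- **If net arm-level:** say so, and remove the 50% compliance clause.

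Keep the intention-to-treat analysis of all eligible admissions as primary. Optionally, pre-specify a supporting analysis of patients flagged by the same algorithm, run identically at all 12 hospitals, who are on an ESA at 48 h. This reduces only the candidate-share dilution. Compliance and usual-care de-escalation would still dilute the 1 day, and the flag covers negative cultures, not stability.

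The cost is a recalculation and a few sentences. The analysis plan already calls for prior-year ESA data on patients who would have met study criteria, though the candidate share and usual-care rate may need a further extract. No patients are added; the stated power may become less favourable.

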## Discussion

Our large, multicenter 2 × 2 factorial cluster-randomized controlled trial will be the first to assess two strategies for reducing ESA use in patients with CAP: (a) routine rapid diagnostic testing at admission and (b) pharmacist-led de-escalation after 48 h for clinically stable patients with negative cultures. The size and randomized design of our study will allow us to establish causality between the interventions and the duration of antimicrobial exposure. The resultant reduction in antibiotic exposure should allow us to test the relationship between ESA exposure and adverse outcomes such as CDI and AKI. By demonstrating the safety of de-escalation and the harms of prolonged ESA exposure, we hope to provide strong evidence supporting the ATS/IDSA recommendations on antimicrobial de-escalation and diagnostic testing, thereby promoting their adoption by clinicians.

The study has several limitations, addressed by its design. First, physicians may resist pharmacist recommendations for de-escalation. To mitigate this, we have secured support from senior leadership at the hospital and departmental levels. Educational efforts will target all participating physicians in the intervention hospitals, and those with low adherence levels will receive feedback and targeted education from the site champion. Second, capturing secondary events, particularly those occurring after discharge, may prove difficult. To address this, we will ascertain patients' vital status from the EHR, Ohio State Death Index, or other existing registries in CCHS. Lastly, uncertainties surrounding the COVID-19 pandemic’s impact on our study exist. If the pandemic intensifies again during the study, the circulation of influenza/RSV may be affected. Even if the pandemic remains under control, infection control measures may persist (e.g., masking and social distancing during respiratory virus season, and improved ventilation). To accommodate these potential changes, our trial will include at least the two most prevalent causes of CAP, and we may consider adding other rapid diagnostic tests (e.g., atypical CAP pathogens and other viruses) if economically feasible, such as when available in a single panel at no increased cost.

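### The power of more than 99% stated for CDI and AKI does not follow from the plan's own inputs (about 20–25% for CDI, 78–89% for AKI), and the plan does not say how the 50% compliance enters any Aim 2 power

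*Protocol article*

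**What the plan says.** All of this stands in the protocol article under Sample size and power analysis.

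- **Aim 1** sets the sample size: "we anticipate an average reduction of 0.3 days (SD = 3.5 days) of exposure to ESAs due to rapid diagnostic testing". The section continues: "To achieve 83% power to detect this effect size at a two-sided alpha of 0.05 and an intra-cluster correlation (ICC) of 0.001", 12 hospitals will be randomized, 6 per arm, averaging 1000 patients each with a coefficient of variation of 0.4. That makes 6000 patients per arm.
- **Aim 2** uses the same hospitals: "we will compare the six hospitals implementing pharmacist-led antimicrobial de-escalation and the other six hospitals serving as the control group". The effect is given as follows: "De-escalation is expected to reduce exposure to ESAs by 1 day (SD = 3), based on our preliminary data". Then: "Assuming a 50% compliance rate in the de-escalation arm, we will have" more than 99% power for this effect size, at two-sided 0.05 and an ICC of 0.005.
- **CDI and AKI** follow in the next sentence, again with more than 99% "power to detect a reduction in the rates of CDI from 1 to 0.5% and AKI from 6 to 3%, under the same assumptions".

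The section does not say whether the 1 day, or the rates of 0.5% and 3%, already allow for half the arm not complying.

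**The concern.** An ICC of 0.005 with 1000 patients per hospital inflates the variance about six-fold or more, so 6000 patients per arm carry the information of roughly 900 to 1000 independent ones. That is little for an event with a 1% rate, and more than 99% power to detect a halving looks implausible on sight.

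CDI and AKI are the harms of prolonged ESA exposure that the trial hopes to show it can reduce. The Discussion expects that the reduced exposure "should allow us to test the relationship between ESA exposure and adverse outcomes such as CDI and AKI". That sentence makes no power claim, but it shows the weight placed on these outcomes. If the protocol says the CDI comparison has more than 99% power, a non-significant result invites the conclusion that de-escalation does not affect CDI. At about 20% power, a true halving would be missed about four times in five.

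The compliance assumption raises a separate question. It is stated but not visibly used, and the result depends on how it is used.

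**Working it through.** **Inputs.** Six hospitals per arm, mean cluster size m = 1000, CV = 0.4, two-sided alpha 0.05. ICC is 0.001 for Aim 1 and 0.005 for Aim 2. The mean size and CV are stated under Aim 1 and carried over, since Aim 2 compares the same 12 hospitals.

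**Formulas.** Two standard corrections for unequal cluster size are used, to give a range.
- A (relative efficiency): DE = [1 + (m − 1)·ICC] / RE, where RE = 1 − CV²·L·(1 − L) and L = m·ICC / [1 + (m − 1)·ICC].
- B: DE = 1 + [(1 + CV²)·m − 1]·ICC.

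Effective n per arm = 6000 / DE. SE = √[(v₁ + v₂) / n], where v is the variance in each arm (SD², or p(1 − p) for a rate). Power comes from the ratio effect/SE, with a noncentral t on 12 − 2 = 10 df or with the normal approximation.

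**Step 1: reproduce Aim 1.** At ICC 0.001, A gives DE = 1.999 / 0.960 = 2.08 and n = 2881. SE = √(2 × 3.5² / 2881) = 0.0922, and 0.3 / 0.0922 = 3.25. Power is 83.4% by t, against the stated 83%. B with t gives 82.1%. The normal approximation gives 89–90% and does not reproduce the stated figure.

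**Step 2: design effect at ICC 0.005.** A: 5.995 / 0.978 = 6.13, n = 979. B: 1 + (1160 − 1) × 0.005 = 6.80, n = 883.

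**Step 3: CDI, 1% to 0.5%.** Variance sum = 0.01 × 0.99 + 0.005 × 0.995 = 0.014875. SE = √(0.014875 / 979) = 0.0039 (A) or √(0.014875 / 883) = 0.0041 (B). The effect of 0.005 is 1.28 or 1.22 SE. Power is 20–21% (t) or 23–25% (normal).

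**Step 4: AKI, 6% to 3%.** Variance sum = 0.06 × 0.94 + 0.03 × 0.97 = 0.0855. SE = 0.0093 (A) or 0.0098 (B). The effect of 0.03 is 3.21 or 3.05 SE. Power is 78–82% (t) or 86–89% (normal).

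**Step 5: could another choice give more than 99%?**
- CDI with no clustering (n = 6000): SE = √(0.014875 / 6000) = 0.00157, ratio 3.18, power 89% (normal). A one-sided test without clustering gives 94%.
- CDI at ICC 0.005 with unlimited patients per hospital: effective n tends to 6 / 0.005 = 1200, and power to 25–30%.
- AKI at the Aim 1 ICC of 0.001: 99.8% or more. Ignoring clustering also gives more than 99%. Neither is the stated assumption.
- An arcsine version at ICC 0.005 gives 25% for CDI and 90% for AKI.

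**Step 6: the 50% compliance.** If the stated effects are net of compliance, steps 3 and 4 stand. ESA days then give SE = √(2 × 9 / n) = 0.136 (A) or 0.143 (B), a ratio of 7.4 or 7.0, and power above 99.9%. If compliance halves each effect:

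| Outcome | Halved effect | Effect/SE | Power, t (10 df) | Power, normal |
|---|---|---|---|---|
| ESA days | 0.5 day | 3.50–3.69 | 88–91% | 94–96% |
| CDI | 1% to 0.75% | 0.56–0.59 | 8% | 9% |
| AKI | 6% to 4.5% | 1.41–1.49 | 25–27% | 29–32% |

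The rates 0.75% and 4.5% are not in the protocol. They follow only from this second reading.

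**The case against.** **The Aim 2 primary power is not shown to be wrong.** A reader might infer that the figure for ESA days is also an error, because half-compliance turns 1 day into 0.5 day. The text does not establish this. It claims power to detect the stated effect size, and the 1 day can be read as the difference between arms after compliance. On that reading more than 99% is correct. On the other, the comparison still has 88–96%. This objection stands: the point here is an ambiguity.

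**The lowest CDI and AKI figures need an added assumption.** A reader might take 8–9% and 25–32% as the trial's power. The stated rates can equally be the arm-level rates to be compared, and halving the differences again is an interpretation. This also stands, so those figures are conditional.

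**The test is not named for proportions.** Aim 1 identifies a t-test on 10 df for means. It does not prove that the same procedure was used for rates, which is why the normal results are shown beside the t results. Neither approaches 99%.

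**AKI is a milder case than CDI.** This is true. The AKI claim fails because of the ICC of 0.005 and would hold at 0.001. But the sentence carries over the Aim 2 assumptions, and those include 0.005.

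**These are secondary outcomes, and a full protocol or analysis plan may say more.** Secondary status limits the consequence: the 12,000 patients come from Aim 1, and the sample size is not called into question. The second part does not help, because the article itself states the inputs and a result that they do not give.

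**Conclusion.** The stated power of more than 99% is wrong for CDI and for AKI, whichever way compliance is read. At the plan's own inputs it is about 20–25% for CDI and about 78–89% for AKI, the ranges covering two corrections for unequal cluster size and both the t and normal tests. For CDI no ICC can produce the claim, since 89% is the two-sided figure with no clustering at all. For AKI it would take a smaller ICC than the one stated.

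These results assume that the Aim 1 cluster size and COV apply to Aim 2 and that the ICC of 0.005 applies to the binary outcomes, as the section's wording implies.

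For ESA days the document supports only the finding that the role of the 50% compliance is unstated. It does not support calling that figure wrong, and it does not support any claim that the trial is too small for its primary outcome.

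**What to change.** In Sample size and power analysis:

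1. Replace the more-than-99% figure for CDI and AKI with the recomputed powers (about 20–25% and about 78–89% if the rates are net of compliance), and name the test used. If a different ICC was meant for AKI, state it and its basis. No such change rescues CDI.
2. Say whether the 1 day and the rates of 0.5% and 3% are before or after the 50% compliance. If before, restate power as about 88–91% (t) or 94–96% (normal) for ESA days, about 8–9% for CDI and about 25–32% for AKI.
3. Describe CDI as an outcome estimated with a confidence interval, and AKI likewise if compliance dilutes its effect, so that a non-significant result is not taken as evidence of no effect.

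The cost is wording only. Sample size, randomization and analysis are unchanged, and the one drawback is that the published figures become less favourable.
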